## Abstract

**Background:**

Prediabetes describes a state of hyperglycemia outside of normal limits that does not meet the criteria for diabetes diagnosis, is generally symptomless, and affects an estimated 38% of adults in the United States. Prediabetes typically precedes the diagnosis of type 2 diabetes, which accounts for increased morbidity and mortality. Although the use of dietary and herbal supplements is popular worldwide, and a variety of single herbal medicines have been examined for glycemic management, the potential of increasingly common polyherbal formulations to return glycemic parameters to normal ranges among adults with prediabetes remains largely unexplored. The purpose of this study is to evaluate the efficacy of a commercially available, polyherbal dietary supplement on glycemic and lipid parameters in prediabetic individuals.

**Methods:**

In this multi-site, double-blinded, randomized controlled clinical trial, 40 participants with prediabetes will be randomized to either a daily oral polyherbal dietary supplement (GlucoSupreme™ Herbal; Designs for Health®, Suffield, CT, USA; containing cinnamon bark (*Cinnamomum cassia*), banaba leaf (*Lagerstroemia speciosa* standardized to 1% corosolic acid), kudzu root (*Pueraria lobata* standardized to 40% isoflavones), fenugreek seed (*Trigonella foenum-graceum* standardized to 60% saponins), gymnema leaf (*Gymnema sylvestre* standardized to 25% gymnemic acid), American ginseng root (*Panax quinquefolius* standardized to 5% ginsenosides), and berberine HCl derived from bark (*Berberis aristata*)) or placebo for 12 weeks. Short-, medium-, and comparatively long-term markers of glycemic control (blood glucose and fasting insulin, fructosamine, and glycated hemoglobin/A1c, respectively), and other glycemic parameters (GlycoMark, β-cell function, and insulin sensitivity/resistance) will be obtained. Lipid profile (total cholesterol, LDL, HDL, and triglycerides), inflammation (hs-CRP), progression to type 2 diabetes mellitus, as well as safety indices (ALT, AST) will be obtained. An intention-to-treat analysis will be used to assess changes in study outcomes.

**Discussion:**

Treatment options for adults with prediabetes are currently limited. This study aims to evaluate the safety and efficacy of a commercially available dietary supplement in the popular, but as yet insufficiently studied, category of polyherbal formulas for the management of glycemic parameters and other biomarkers associated with prediabetes.

**Trial registration:**

ClinicalTrials.gov, ID: NCT03388762. Retrospectively registered on 4 January 2018.

**Electronic supplementary material:**

The online version of this article (10.1186/s13063-018-3032-6) contains supplementary material, which is available to authorized users.

## Background

Prediabetes, a disorder for which global prevalence is rapidly increasing [1], affects 38% of people in the United States [2]. People with prediabetes present with slightly elevated glucose levels (i.e., fasting plasma glucose between 100 and 125 mg/dL, glycated hemoglobin/A1c (HbA_1c_) between 5.7 and 6.4%, or postprandial glucose between 140 and 199 mg/dL), but not high enough to be considered type 2 diabetes (T2D) [3]. People with prediabetes often do not display physical symptoms; however, prediabetes perpetuates pancreatic β-cell dysfunction [4] and nearly always precedes diagnosis of T2D [3], a disease affecting approximately 9% of adults in the United States [5]. Prediabetes and T2D is often accompanied by comorbid low HDL (high-density lipoprotein) cholesterol and high triglycerides, and is responsible for increased risk of macrovascular disease such as heart disease and stroke. T2D further increases risk for microvascular disease such as retinopathy (which may lead to blindness and other visual problems), nephropathy (which may lead to kidney failure), neuropathy (a leading cause of amputation), and death [2, 6, 5].

Current recommendations for managing prediabetes and preventing progression to T2D remain limited due to very few pharmacological options with favorable safety profiles [7, 8] and the challenges posed in successful implementation and maintenance of certain lifestyle modifications (i.e., increased physical activity, diet, and weight loss) [3, 9].

A number of herbs have been used to manage symptoms related to deleterious changes in glucose metabolism [10–17]. A number of clinical studies of herbal interventions (i.e., cinnamon, fenugreek, banaba, curcumin, and others) conducted among adult populations with prediabetes have demonstrated improved glycemic control, particularly with regard to reducing fasting blood glucose [18–25] and postprandial glucose [18, 22, 26–29], HbA_1c_ [25, 30, 31], fasting insulin levels [9, 26, 28–31], homeostatic model of Insulin Resistance (HOMA-IR) [20, 28, 30, 32, 33], and increasing homeostatic model of β-cell function (HOMA-β) [27, 32]. Substantial changes in glycemic parameters typically occur within 12 weeks [34, 35]. Likewise, each of these outcomes have demonstrated significant changes over a 12-week duration in previous trials [19, 20, 22, 28, 29, 33, 36].

Several herbs have also demonstrated benefit in glycemic control in clinical trials among T2D populations. These herbs and herbal extracts include berberine [37–39], ginseng [40, 41], gymnema [42, 43], banaba [44], cinnamon [24, 45], fenugreek [46], and kudzu [47]. Of these, some have also demonstrated potential benefit for promoting positive changes in lipid markers [37, 48–60].

Each of these seven plant ingredients may improve glycemic control, and all have a wide history of ethnobotanical use in raw unprocessed, crudely processed, or other preparations [15, 17, 61]. Approximately 80% of the total content of free amino acids in fenugreek seeds is represented by 4-hydroxyisoleucine, and appears to directly stimulate insulin in a glucose-dependent manner [62–65]. Likewise, in vitro research suggests that some active constituents of the banaba leaf have an insulin-like effect [66, 67]. Lagerstroemin, an ellagitannin present in banaba, may activate insulin receptors [44, 65, 66, 68]. In addition, kudzu likely increases glucose utilization [69] and activates alpha-1 adrenoceptors in the adrenal gland to enhance the secretion of beta-endorphin, resulting in decreased plasma glucose [70]. Gymnema leaves contain oleanane triterpene saponins, which include gymnemic acids [71]. Gymnemic acids appear to reduce intestinal absorption of glucose and may stimulate pancreatic β-cell growth [72, 73]. Gymnema may also have a direct effect on β-cell function, thus resulting in the release of insulin [74]. Further, gymnema may also increase serum C-peptide levels, indicative of a potential increase in endogenous insulin secretion [43].

Other plant ingredients in GlucoSupreme™ Herbal, a commercially available polyherbal dietary supplement, may be responsible for similar mechanisms of action. Polyphenolic polymers, found in cinnamon, appear to potentiate insulin action by increasing phosphorylation of the insulin receptor, thereby increasing insulin sensitivity, which may lead to improvements in blood glucose control and lipid levels. Cinnamon extracts also appear to activate glycogen synthetase and increase glucose uptake [75–77]. Berberine, another ingredient present in the study treatment, stimulates glucose transport through a mechanism distinct from insulin via increasing GLUT1 activity [78], and improves glucose metabolism through induction of glycolysis related to the inhibition of glucose oxidation in mitochondria. Berberine-induced AMPK activation is likely a consequence of mitochondrial inhibition that increases the AMP/ATP ratio [38]. Thus, at least some of berberine’s potential effects in the treatment of diabetes derive from stimulation of AMPK activity [79]. Berberine also enhances signaling, notably through increased glucose transporter-4 translocation into the plasma membrane via the enhancement of insulin signaling pathways and insulin receptor substrate-1-phosphoinositide 3-kinase-Akt. In addition, berberine appears to increase glucose-stimulated insulin secretion and proliferation in Min6 cells via an enhanced insulin/insulin-like growth factor-1 signaling cascade. Berberine likely decreases glucose absorption through the intestinal epithelium in part due to its ability to inhibit alpha-glucosidase [80], and may act as an effective insulin-sensitizing and insulinotropic treatment [81]. The chemical structure of berberine and related isoquinoline alkoloids differs from other commonly used hypoglycemic agents, such as sulfonylureas, biguanides, thiazolidinediones (TZDs), and acarbose [38].

Ginsenosides are triterpenoid saponins and the major active constituents of ginseng [82], and target different types of tissues, producing metabolic and other pharmacological responses [40, 83]. Antidiabetic effects demonstrated by ginsenosides present in American ginseng root, including Rb_1_ [40, 83, 84], are likely related to their ability to activate peroxisome PPAR-γ, which is responsible for regulation of expression of key genes involved in lipid and glucose metabolism and adipocyte differentiation [83, 85, 86]. The activation of PPAR-γ causes body-wide lipid repartitioning by increasing the triglyceride content in adipose tissue and lowering free fatty acids in circulation, liver, and muscle, thus leading to improvements in insulin sensitivity [40, 83, 87]. Likewise, the transcriptional response of PPAR-γ may result in the recruitment of cofactors which increase insulin-stimulated glucose uptake, and positively regulate glucose metabolism and energy expenditure [83, 88, 89].

TZDs are full PPAR-γ agonists [90] often prescribed in the clinical treatment of T2D, but often result in undesirable side effects [83, 91, 92]. Alternately, the potential antidiabetic effects of the partial PPAR-γ agonist ginsenoside Rb_1_ is exemplified through the promotion of adipocyte differentiation via PPAR-γ activation and increased activation of glucose transporter 4 (GLUT4) associated with insulin sensitivity in adipocyte tissue [83, 84, 87]. Therefore, American ginseng may improve insulin resistance by reducing lipotoxicity in muscle and liver through increasing the ability to store lipids in adipocytes, and enhance insulin sensitivity through increase of adipocyte GLUT4 expression [83].

While many of these herbs appear to be promising when used in isolation, the practice of herbal medicine most often utilizes polyherbal combinations for purported synergistic effects [82]. Although a handful of polyherbal dietary supplement formulations [9, 20, 21, 33, 93, 94] have been examined for the improvement of glycemic control among prediabetic populations, no study has yet examined the potential impacts of berberine, ginseng, gymnema, banaba, cinnamon, fenugreek, and kudzu as a polyherbal formulation using a comprehensive panel of validated markers of lipid status and glycemic control (i.e., short-term, medium-term, and longer-term) utilized in both research and clinical practice.

In light of the vast number of commercially available, polyherbal formulas that have not yet been studied, rigorous clinical trials are needed to evaluate the efficacy of commercially available, polyherbal dietary supplements. This remains an especially important research gap since the dosages and ingredients in these formulas are highly heterogeneous and have not been well-examined.

## Methods

### Objectives

The primary objective of this study is to evaluate the impact of a commercially available, polyherbal dietary supplement on markers of glycemic control among a sample of adults with prediabetes. The secondary objectives are to investigate the effects of this supplement on lipid and inflammatory markers.

### Research type

A 12-week, randomized, double-blinded, placebo-controlled clinical trial is being conducted to achieve the objectives of this study. The authors hypothesize that GlucoSupreme™ Herbal will improve a variety of validated markers of glycemic control more effectively than placebo. In accordance with previous studies of dietary supplements among prediabetic adults and the interval between measurements of glycemic control in clinical practice, this proof-of-concept and exploratory study is 12 weeks in duration.

### Participants

#### Screening of participants

Key entry criteria are adults who satisfy one or more American Diabetes Association (ADA) criteria for prediabetes, and do not include those diagnosed with diabetes. Among other criteria provided in Table 1, daily tobacco smokers were excluded due to unknown safety interactions with nutritional components in the study treatment. Previous research demonstrated an increased risk of lung cancer in smokers consuming β-carotene dietary supplements [95], and β-carotene is naturally present and sometimes highly abundant in many plants, including kudzu [96].

**Table 1 Tab1:** Inclusion and exclusion criteria

Critera	
Inclusion	Exclusion
Aged ≥18 years Fulfill prediabetes’ diagnostic criteria, determined by blood measurement values obtained within past 12 weeks Agree to continue with current diet and refrain from taking any new nutritional or herbal supplements during the study Agree to continue with current physical activity level throughout study period Able to understand and write English Voluntarily consent to the study and understand its nature and purpose including potential risks and side effects	Current daily use of any oral hypoglycemic medication or insulin injection Any current or previous diagnosis of diabetes (type 1 or type 2) Current daily use of any supplement containing the herbs in the study supplement Known allergies to any substance in the study supplement Current daily tobacco smoker Currently pregnant or breastfeeding, or planning to become pregnant in the next 12 weeks Myocardial infarction, vascular surgery, or stroke in the past year Refusal to provide consent for the study

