##### Diagnostic criteria

Prediabetes is classified as demonstrating any of the following, according to ADA guidelines [3, 97]:Hemoglobin A1c (HbA_1c_) of 5.7–6.4%Fasting blood glucose of 100–125 mg/dL2-h 75-g Oral Glucose Tolerance Test blood glucose value of 140–199 mg/dL 

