##### Source of participants

Study participants will be identified and recruited from community health fairs, diabetes support groups, and directly from clinicians in University of Maryland Medical System outpatient facilities (Baltimore, MD, USA), including the Center for Diabetes and Endocrinology, and Family Medicine Associates. Alliance Integrative Medicine (Cincinnati, OH, USA), and a population of Amish research participants (Lancaster, PA, USA) will serve as additional sources. A member of the research team will screen and include participants via physician referral and/or by verification of laboratory parameters (fasting plasma glucose: 100–125 mg/dL and/or HbA_1c_: 5.7–6.4% and/or postprandial glucose: 140–199 mg/dL), indicating prediabetes status within past 12 weeks, according to ADA guidelines [3]. Male and female participants will be eligible to participate. Based on the racial and ethnic diversity across all sites, a racially and ethnically diverse study population is anticipated.

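### The entry rule sets no upper limit on the other glycemic markers, so an undiagnosed person already in the diabetic range can be randomised and then counted as progression to T2D

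*Protocol article*

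**What the plan says.** All of this is in the protocol article.

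- **Target population.** The Abstract describes prediabetes as hyperglycemia short of the diagnostic criteria for diabetes. The Background describes glucose that is raised "but not high enough to be considered type 2 diabetes (T2D").
- **Entry rule.** Under Screening of participants, the trial takes "adults who satisfy one or more American Diabetes Association (ADA) criteria for prediabetes, and do not include those diagnosed with diabetes". Under Diagnostic criteria, "Prediabetes is classified as demonstrating any of the following, according to ADA guidelines": HbA1c 5.7–6.4%, fasting glucose 100–125 mg/dL, or 2-hour OGTT glucose 140–199 mg/dL. Source of participants joins the same ranges with and/or, and lets staff "screen and include participants via physician referral and/or by verification of laboratory parameters".
- **Age of the value.** Table 1 has prediabetes status "determined by blood measurement values obtained within past 12 weeks".
- **Exclusions that touch diabetes.** There are two in Table 1: "Any current or previous diagnosis of diabetes (type 1 or type 2") and "Current daily use of any oral hypoglycemic medication or insulin injection".
- **Baseline blood.** It is drawn from everyone at the first visit. No stated eligibility condition uses the result.
- **Outcome.** Progression to T2D by the 2016 ADA criteria is a secondary outcome (Table 2). Additional indicators defines incidence as diabetes cases at end of study over all participants in the group, times 100%.

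**The concern.** The definition of the population and the rule for entering it do not match. The definition has a ceiling: the person must be below diabetes. The rule has a ceiling only on the one marker used to qualify, and none on the other markers or on the blood drawn at baseline. The two exclusions depend on someone having already made a diagnosis or started treatment, so neither catches a person whose diabetes has not been recognised.

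Two things are at stake. The randomised sample may include people outside the population that the conclusions are meant for. And the progression outcome cannot tell a case that arose during the 12 weeks from one present on day one. With arms of 20, one such person is visible in the result.

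**Working it through.** **Step 1. The plan's own figure.** The only figure needed is the arm size. Sample size gives 20 per arm from a 0.91 SD difference, two-sided alpha 0.05, an equal-variance t test and 80% power. The exact noncentral t calculation with 20 per arm at 0.91 SD gives power 0.801, so the figure reproduces. A laboratory ceiling at entry does not change it.

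**Step 2. Does the stated rule admit such a person?** Two constructed cases, not taken from the document:

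| Check | Case A: fasting glucose 112 mg/dL, HbA1c 6.9%, no diagnosis, untreated | Case B: HbA1c 6.3% ten weeks ago, baseline HbA1c now above 6.4%, no diagnosis, untreated |
|---|---|---|
| One marker in a prediabetes range | Yes (112 is within 100–125) | Yes (6.3 is within 5.7–6.4) |
| Value no older than 12 weeks | Yes, if recent | Yes |
| Excluded by diagnosis | No | No |
| Excluded by daily glucose-lowering treatment | No | No |
| Excluded by a limit on another marker | No such criterion | No such criterion |
| Excluded by the baseline result | No such criterion | No such criterion |
| Below diabetes, as the Background requires | HbA1c is above the prediabetes ceiling | Baseline HbA1c is above the prediabetes ceiling |

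Both pass every stated glycemic entry check and fail the definition.

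**Step 3. Effect on the incidence outcome.** Stated formula: incidence = end-of-study cases / all in group × 100%.

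Take an arm of 20 with no new case during follow-up and one participant in the diabetic range at both baseline and week 12:

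- as stated: 1/20 × 100% = 5%;
- restricted to those below the range at baseline: 0/19 × 100% = 0%.

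Each further such person adds another 5 points. With 22 randomised per arm (44/2) the step is 1/22 = 4.5 points. If there is one such person in the whole trial, the arms differ by about 5 points with no progression in either.

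**Step 4. How often might this occur?** The document gives no share of such entrants, so the share q below is an assumption, with a range. Among 40 participants, the expected number is 40q and the chance of at least one is 1 − (1 − q)^40.

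| Assumed q | Expected among 40 | Expected per arm of 20 | Chance of at least one |
|---|---|---|---|
| 2% | 0.8 | 0.4 | 55% |
| 5% | 2 | 1 | 87% |
| 10% | 4 | 2 | 99% |

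These figures show only that a small share would be enough to matter. They do not estimate how many will enter.

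**The case against.** **The intent is clear and the article is condensed.** The article speaks of key criteria, defers to ADA guidelines, and twice describes prediabetes as below diabetes. A clinician who saw a diabetic-range value might make a diagnosis, which would trigger the exclusion. Handling of discordant markers could sit in a fuller protocol. Whether a single unconfirmed value counts as diabetes depends on a guideline that is not reproduced. All of this is fair and lowers the likely number of such entrants. It does not remove the point: the criteria as printed, followed to the letter, admit these people, and no stated rule requires anyone to check the other markers or the baseline blood.

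**Randomisation protects the comparison.** It does, from systematic bias, and the study calls itself proof-of-concept and exploratory. But chance imbalance of one person is 5 points on this outcome, and the level of incidence in each arm is overstated regardless.

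**Stronger readings that the document does not support.**

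- A reader might infer a large loss of power from a few extreme HbA1c values. The document gives no HbA1c SD, and 0.91 SD is stated for continuous variables in general. Any power figure would therefore rest on an invented distribution. It would also apply only to an unadjusted t test on week-12 values, whereas Statistical analysis methods also plans a mixed model over the 12 weeks. A participant who is high but stable adds between-person spread, which largely drops out of within-person change.
- A reader might infer that the 12-week limit on laboratory values conflicts with the screening period of plus or minus 3 days. It does not: a ten-week-old value reviewed two days before the start satisfies both. The plus-or-minus wording is an editorial matter.
- A reader might want a qualifying value on the baseline sample, or supply held until it is read. The first would also exclude people whose baseline is now normal. The second could need another contact in a two-visit trial. Neither is needed to close this gap.

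**Conclusion.** The point holds as a defect in the stated entry rule and in the progression outcome that depends on it. The rule admits undiagnosed, untreated people with another marker, or a baseline sample, above the prediabetes range, contrary to the population that the article defines. The incidence formula then reports them as progression if they are still in range at week 12.

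The size is about 5 percentage points per person in an arm of 20. This assumes that the person stays in the diabetic range and meets the 2016 ADA criteria as the trial applies them. How many such people enter is unknown from the document.

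The effect on the primary glycemic outcomes is mainly one of interpretation: the sample may not be purely prediabetic. The document does not support a stated loss of power or a claim that the sample size is wrong. It also does not show that anyone with unrecognised diabetes has been enrolled, only that the rule permits it.

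**What to change.** 1. **Table 1.** Add that no available screening glycemic value may lie above the upper limits already printed under Diagnostic criteria and Source of participants (HbA1c 6.4%, fasting glucose 125 mg/dL, 2-hour OGTT glucose 199 mg/dL), whether or not diabetes has been diagnosed.
2. **Additional indicators.** Count T2D incidence only among participants below the diabetic range at baseline, in both numerator and denominator. Report separately, by arm, how many were in that range at baseline.
3. **Statistical analysis methods.** Pre-specify a sensitivity analysis of the primary glycemic outcomes without participants whose baseline sample proves to be above those limits. Keep them in the main ITT analysis.

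The cost is a few more screen failures, one extra analysis and an IRB amendment. The baseline tests are already drawn. Recruitment was under way when the article was submitted, so the first change helps only later entrants, while the second and third cover everyone. The care of a participant found to be in that range is for the site physicians and is outside this point.

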Other relevant glycemic parameters required to gain a well-rounded understanding regarding potential impacts of the intervention include fructosamine and GlycoMark. Fructosamine is the concentration of plasma glucose over the lifetime of the protein, and represents the degree of glycation in many serum proteins involved in glucose synthesis. It is a test utilized in clinical practice and clinical studies of natural products [31, 110], is often viewed as an adjunct to HbA_1c_ (a measurement which is recommended every 3 months in clinical practice and reflects longer-term glycemic change over several months [34]) and fasting glucose measurements (short-term glycemic change), and reflects intermediate-term (previous 2–3 weeks) glycemic change. GlycoMark, a blood test used in clinical practice to determine peak hyperglycemia, provides accurate recognition of recent glycemic deterioration or improvement (within the previous 1–2 weeks) [111–113].

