#### Bias control

All dietary supplements and medications taken by participants during the study period are recorded and analyzed at the conclusion of the study. The daily use of oral hypoglycemic medications or insulin injections during the study period is considered an exclusion criterion during screening and prohibited during the study, resulting in exclusion from the per-protocol analysis, should it occur. Broad changes in dietary intake and physical activity are recorded at each time point in order to account for potential bias.

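### The herb exclusion covers only current daily use and the on-study rule only new supplements, so existing non-daily users of a study ingredient can enter and continue in either arm

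*Protocol article*

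**What the plan says.** Three places in the protocol article govern background use of the study ingredients.

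- **Table 1, exclusion.** The herb criterion is "Current daily use of any supplement containing the herbs in the study supplement". It gives no look-back period.
- **Table 1, inclusion.** Participants agree to "refrain from taking any new nutritional or herbal supplements during the study". Supplements already in use are not covered.
- **Bias control.** "All dietary supplements and medications taken by participants during the study period are recorded and analyzed at the conclusion of the study". The section Polyherbal dietary supplement intervention adds a daily diary of changes in medication and supplement use. Neither section attaches a consequence to taking the study herbs.

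The per-protocol definition (Analysis of datasets) requires that inclusion criteria are met, that dosing compliance lies between 75 and 107%, that laboratory assessments are complete, and that primary outcomes are measured on time. It does not mention concurrent use of the study ingredients. The primary analysis is by intention to treat.

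The drug criterion has a similar form: "Current daily use of any oral hypoglycemic medication or insulin injection". Bias control repeats the daily, oral-or-insulin limit for the study period, with removal from the per-protocol analysis as the consequence. Table 1 separately excludes "Any current or previous diagnosis of diabetes (type 1 or type 2)".

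**The concern.** The trial is meant to compare the seven-ingredient product with no such product. Read together, the two supplement rules leave a gap between them: a person who takes one of the seven ingredients regularly but not every day passes the exclusion, and continuing is not a new supplement.

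The Background section states that each of the seven ingredients may improve glycemic control. On that premise, a placebo participant who keeps taking one is partly treated, and an active-arm participant who was already taking one may have less to gain. Either way the between-arm difference shrinks. A mixture of users and non-users also adds variance.

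Such users are plausible on the protocol's own account. Source of participants names an integrative medicine practice among the sites and diabetes support groups among the recruitment routes, and the Discussion says that more than half of American adults take a dietary supplement and that glycemic control is a common goal. With 20 per arm, a few such participants, or a chance imbalance in them, can matter.

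**Working it through.** **1. Does any rule close the gap?** Take a person who uses berberine capsules several days a week before and during the trial.

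| Rule | Effect on this person |
|---|---|
| Table 1 herb exclusion (current daily use) | Not excluded: use is not daily |
| Table 1 supplement commitment (new supplements) | Not breached: the supplement is not new |
| Per-protocol definition (Analysis of datasets) | Not removed: no criterion on study ingredients |
| Bias control, rule on glucose-lowering drugs | Does not apply: covers drugs, not herbs |
| Diary and recording of supplements | Use is captured, with no stated consequence |

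Under the stated rules, this person is analysed in both the intention-to-treat and the per-protocol sets.

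**2. The plan's own sample size.** Inputs from the section Sample size: difference 0.91 SD, two-sided alpha 0.05, two-sample equal-variance t test, 80% power, 20 per arm. Solving the noncentral t power equation for the arm size gives 19.96, so 20 per arm and 40 in total. Power at 20 per arm is 80.1%. The stated figure is reproduced.

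**3. Illustration of dilution.** The documents give neither a rate of herb use nor the effect of intermittent use, so both are assumptions:

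- p = share of participants affected: 5%, 10%, 20%.
- L = fraction of the contrast that each affected participant loses: 0.5 or 1.
- The SD is held unchanged.

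Diluted effect = 0.91 × (1 − p × L). Power is for 20 per arm, same test.

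| p | L = 0.5: effect (SD) | Power | L = 1: effect (SD) | Power |
|---|---|---|---|---|
| 5% | 0.91 × 0.975 = 0.887 | 78% | 0.91 × 0.95 = 0.864 | 76% |
| 10% | 0.91 × 0.95 = 0.864 | 76% | 0.91 × 0.90 = 0.819 | 71% |
| 20% | 0.91 × 0.90 = 0.819 | 71% | 0.91 × 0.80 = 0.728 | 61% |

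The L = 1 column requires that intermittent use of perhaps one ingredient does as much as the full daily product, so it is a worst case.

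**The case against.** The strongest reply is that the plan holds background habits constant (current diet, current activity, nothing new added) and tests the product on top of them. Randomisation balances stable background use in expectation, use is recorded, and the trial describes itself as proof-of-concept and exploratory. Part of this stands: the comparison remains valid as a randomised one, and the harm is dilution and noise rather than systematic bias. But an add-on comparison does not fit well with excluding daily users of the same herbs. That exclusion shows that the investigators want participants free of them, and the word *daily* defeats the purpose. Nor is this detail left to a fuller document, because the article states the limit itself.

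Three stronger readings are tempting, and the documents do not support them.

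- **That placebo participants in general may take the study herbs.** Current daily users are excluded and starting a new supplement is barred. On-study exposure through this gap is confined to existing non-daily users.
- **That people who recently stopped a herb or drug erode the treatment effect.** The protocol says HbA1c "reflects longer-term glycemic change over several months", so their baseline may partly reflect earlier use. But the later drift is expected equally in both arms: it adds variance and possible chance imbalance, and the dilution formula does not describe it.
- **That the drug exclusion is an equal weakness.** Anyone with a current or past diabetes diagnosis is already excluded. What remains is glucose-lowering drugs taken without that diagnosis, and nothing in the documents suggests that this group is material.

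**Conclusion.** The point holds for the study herbs. As written, an existing non-daily user of a study ingredient can enter, continue in either arm and stay in the per-protocol set. On the protocol's premise about the individual ingredients, this weakens the contrast that the trial is built to detect.

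The size cannot be derived from the documents. The range of about 78% to 61% power, against 80% planned, rests on an assumed 5 to 20% of participants affected, an assumed loss of half to all of the contrast for each, and an unchanged SD. A loss of less than half, or a lower rate of use, would leave power closer to 80%. This is a cheap improvement, not a flaw that undermines the trial.

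For glucose-lowering drugs, the observation is limited to wording: Table 1 and Bias control confine the restriction to daily oral drugs or insulin.

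**What to change.** - **Table 1, herb exclusion.** Drop *daily*, so that the criterion covers any current use of a supplement containing any of the seven ingredients. Add a look-back period that the investigators choose and justify. The 12-week window in Table 1 concerns the age of the qualifying blood values and is not by itself a justification.
- **Table 1, supplement commitment.** Ask participants to take no supplement containing any of the seven ingredients, and no other new supplement, during the study.
- **Per-protocol definition.** Exclude participants with recorded on-study use of these ingredients outside the assigned product. The diary and the record of supplements already supply the data, including for those enrolled before the change.
- **Glucose-lowering drugs.** Ask the investigators to reconsider the daily, oral-or-insulin wording in Table 1 and Bias control together with the exclusion of diagnosed diabetes. No specific medication rule is proposed here.

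The cost is a slightly smaller recruitment pool and an ethics-approved amendment. Because the trial was recruiting at submission, eligibility and the per-protocol definition would change part-way through, and the date of the change should be reported.
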